### Monitoring of participants and criteria for withdrawal from study

#### Spironolactone treatment

As a safeguard, at the time of enrollment each patient will be asked to identify a primary responsible physician who will be notified of the patient’s enrollment and, therefore, will be aware of the potential development of hyperkalemia or renal insufficiency during the course of the study. Serum potassium, blood urea nitrogen and creatinine will be measured one week after initiating therapy or a dose increase and then serially thereafter according to the pre-specified schedule (Figure 1 and Additional file 1: Figure S1). For laboratory monitoring of serum potassium, blood urea nitrogen and creatinine on day 7, week 6, week 9, week 16 and week 20 (±7 days), participants will be given laboratory requisition slips for sample collection at an outside facility near their home (Additional file 1: Figure S1). Participants will be instructed to have their samples drawn within 7 days of the specified time point. Those participants who wish to return to the NIH Clinical Center to have these samples drawn may do so instead of going to an outside facility. For laboratory monitoring of serum potassium, blood urea nitrogen and creatinine at week 12 and week 24, samples will be collected along with other research samples at the time of the NIH Clinical Center visit (Additional file 1: Figure S1). In the event that specimens are reported as hemolyzed, participants will be instructed to repeat their sample draw within 7 days of their previous sample. In the event that any scheduled laboratory monitoring is delayed for >7 days, participants will be instructed to stop the study drug and will be removed from the protocol.

If while on therapy a patient’s serum potassium level increases to 5.3 to 5.9 mEq/L, the study drug will be stopped and their serum potassium level will be checked again within 24 to 48 hours (Figure 2). At the study investigators’ discretion, any participant with a potassium level ≥5.3 mEq/L can be referred for medical evaluation at the nearest health care facility. If the repeat serum potassium is <5.3 mEq/L, then the study drug will be resumed at the previous dose and serum potassium measurement will be repeated again 72 to 96 hours later, and then weekly for two weeks, followed by resumption of the normal monitoring schedule as long as the serum potassium remains <5.3 mEq/L. If the serum potassium remains ≥5.3 mEq/L on two consecutive blood draws, the study drug will be discontinued. Delay in laboratory monitoring longer than 48 hours from the specified time frame in participants with a serum potassium of ≥5.3 mEq/L will result in that patient being removed from the protocol. If at any time the serum potassium is ≥6.0 mEq/L (Figure 2), the study drug will be discontinued and the participant will be referred to the nearest health care facility where standard treatment for hyperkalemia can be provided. In these participants, the study drug will not be restarted and they will be removed from the protocol. If while on the study drug a participant’s serum creatinine increases >50% then the study drug will be discontinued and the participant will be removed from the protocol. Prior to initiation of the study drug and throughout the trial during follow-up visits, participants will be asked about the presence of breast pain and, in male participants, the development of gynecomastia.

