### Treatment delivery

The total duration of the treatment period will be 24 weeks. Treatment assignment will be double-blinded. Randomization will be computer-generated and participants will be stratified according to the cause of PAH (idiopathic, heritable, and drug or toxin-induced PAH versus disease-associated PAH) and NYHA/WHO classification (I or II versus III; see Table 3). Participants meeting eligibility criteria for enrollment will be randomized to either 25 mg of spironolactone or matching placebo once daily. The NIH Clinical Center Pharmaceutical Development Section will be compounding and monitoring study drug stability. Four different capsules will be prepared: spironolactone 25 mg and matching placebo, and spironolactone 50 mg and matching placebo. If the 25 mg dose of study drug is well tolerated, (that is, potassium remains <5.0 mEq/L and serum creatinine does not increase >50% from baseline at study entry) then the dose will be increased to 50 mg daily following week 6 laboratory monitoring (Figure 1).

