**Figure 1 F1:**
[figure not shown]
**Serum potassium and creatinine monitoring schedule.** *Participants with potassium level ≥5.3 at week 1 will not be eligible for dose increase at 8 weeks. **Throughout the study, participants with potassium level >5.0 will undergo dietary counseling regarding a low potassim diet. Cr, creatinine; K, potassium; labs, laboratory tests.

**Table 3 T3:** New York Heart Association/World Health Organization classification

**Class**	**Symptoms**
I	Patients with pulmonary hypertension but without resulting limitation of physical activity. Ordinary physical activity does not cause undue dyspnea or fatigue, chest pain or near-syncope.
II	Patients with pulmonary hypertension resulting in slight limitation of physical activity. They are comfortable at rest. Ordinary physical activity causes undue dyspnea or fatigue, chest pain or near-syncope.
III	Patients with pulmonary hypertension resulting in marked limitation of physical activity. They are comfortable at rest. Less than ordinary activity causes undue dyspnea or fatigue, chest pain or near-syncope.
IV	Patients with pulmonary hypertension with inability to carry out any physical activity without symptoms. These patients manifest signs of right heart failure. Dyspnea and/or fatigue may even be present at rest. Discomfort is increased by any physical activity.

All participants will receive new study drug in the mail between weeks 7 and 9 of the study. Participants who are not eligible for the dose increase (Figure 1) will also receive new study drug but the dose will be unchanged. The 25 mg and 50 mg dosage formulations will each be a different colored capsule so that the participants and providers can easily discern them. Two different color-matched placebo capsules will be formulated as well. Study coordinators will contact participants and instruct them to begin the new study medication at the appropriate time. Participants will also be instructed to mail their old study medication bottles back to the NIH Clinical Center to avoid confusion with the new study drug.

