### Individual participant stopping rules

PAH is a progressive disease and therefore clinical worsening may occur in participants during the protocol, irrespective of their treatment group assignment. Individual stopping rules for participants enrolled in the protocol include:

1. If a participant develops clinical evidence of right heart failure (which may include but is not limited to elevated jugular venous pressure, ascites and lower extremity edema) as determined by the patient’s primary physician or the investigators, then the participant will be removed from the protocol and treated for decompensated right heart failure according to standard of care.

2. If a participant deteriorates clinically, even in the absence of overt right heart failure, and the primary treating physician or the investigators feel that the addition of a MR antagonist such as spironolactone or eplerenone is clinically indicated then the participant will be removed from the study.

3. If a participant has more than one episode of serious hyperkalemia (potassium ≥5.3 mEq/L) or one episode of severe hyperkalemia (potassium ≥6.0 mEq/L), the study drug will be discontinued and the participant will be removed from the protocol.

4. If a participant develops renal insufficiency (rise in serum creatinine >50% of baseline) while on protocol, then the study drug will be discontinued and the participant will be removed from the protocol.

5. In the event that testing for serum potassium, blood urea nitrogen and creatinine is delayed for >7 days, the participant will be instructed to stop the study drug and will be removed from the protocol.

6. In any participant with a serum potassium level ≥ 5.3 mEq/L, a delay in laboratory monitoring longer than 48 hours from the specified time frame will result in removal from the protocol.

7. If while on study drug a participant develops significant breast pain or gynecomastia then the study drug will be discontinued and the participant will be removed from the protocol.

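### The hyperkalemia stopping rule is worded three ways that do not agree when potassium of 5.3 to 5.9 mEq/L recurs or persists, and the discontinuation endpoint inherits the ambiguity

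*Protocol article*

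**What the plan says.** The protocol article states the consequence of a potassium of 5.3 mEq/L or more in three places.

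- **Spironolactone treatment (monitoring and withdrawal section).** At 5.3 to 5.9, "the study drug will be stopped and their serum potassium level will be checked again within 24 to 48 hours". Then: "If the repeat serum potassium is <5.3 mEq/L, then the study drug will be resumed at the previous dose", with closer follow-up before the normal schedule resumes. Finally: "If the serum potassium remains ≥5.3 mEq/L on two consecutive blood draws, the study drug will be discontinued". Removal from the protocol is stated here for values of 6.0 or more and for a creatinine rise above 50%, but not for two consecutive values of 5.3 or more.
- **Individual participant stopping rules, rule 3.** "If a participant has more than one episode of serious hyperkalemia (potassium ≥5.3 mEq/L) or one episode of severe hyperkalemia" (6.0 or more), drug is discontinued and the participant is removed. *Episode* is not defined.
- **Risks associated with spironolactone therapy.** Drug ceases at 6 or more, or when potassium stays at or above 5.3 on two occasions. The word *consecutive* does not appear, and removal is not mentioned.

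Study endpoints lists, as a secondary safety endpoint, the rate of drug discontinuation for hyperkalemia, identified only by the 5.3 threshold. Study analysis compares discontinuation rates between the arms with Fisher's exact test.

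Two related statements concern the dose increase. Treatment delivery makes it conditional on "potassium remains <5.0 mEq/L and serum creatinine does not increase >50% from baseline at study entry", while the Figure 1 caption says "Participants with potassium level ≥5.3 at week 1 will not be eligible for dose increase at 8 weeks". On timing, "All participants will receive new study drug in the mail between weeks 7 and 9 of the study", and potassium "will be measured one week after initiating therapy or a dose increase".

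**The concern.** Hyperkalemia is among the most significant risks that the article names for spironolactone. The protocol should give one answer to two questions: does drug restart after a second, separate value of 5.3 or more, and does a participant with a persistent value leave the protocol or only stop drug? The three texts do not give one answer to either.

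Two things are at stake. Staff who follow different sections could handle comparable participants differently. And the discontinuation endpoint has no fixed definition: the same potassium record can count as a discontinuation or not. The threshold that triggers a temporary stop is also the one that labels the endpoint. The monitoring section does use different verbs for a temporary stop and a final discontinuation, which suggests that temporary stops are not meant to count, but Study endpoints does not say so.

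**Working it through.** The plan states no figure on this point that could be reproduced. The check applies each text literally to the same potassium sequences (mEq/L).

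| Sequence | Spironolactone treatment section | Stopping rule 3 | Risks section |
|---|---|---|---|
| 5.4, recheck 5.1 | Drug resumed | One episode: continues | One occasion: continues |
| 5.4, recheck 5.1, resumed; later 5.4, recheck 5.1 | Drug resumed both times | Two episodes: discontinued and removed | Stops if any two occasions count; continues if they must be consecutive |
| 5.4, recheck 5.5 | Drug discontinued; removal not stated | Not triggered if the run is one episode; discontinued and removed if each draw is an episode | Drug stops; removal not mentioned |
| 6.1 | Discontinued and removed | Discontinued and removed | Drug stops |

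Rows 1 and 4 agree. Row 2 gives opposite results in the first two texts. In row 3 the drug stops under the monitoring section, but whether the participant is removed depends on an undefined word.

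**Endpoint.** The row 2 participant counts as a discontinuation under rule 3 and not under the monitoring section. The row 1 participant counts only if a temporary stop counts.

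**Scale.** Up to 70 participants are randomized 1:1, so 70 / 2 = 35 per arm if enrollment is full. One reclassified participant moves that arm's rate by 1 / 35 = 2.9 percentage points. The article gives no expected number of participants in rows 2 or 3, so no overall effect on the Fisher test can be derived.

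**Dose-increase criterion.** Take a week-1 potassium of 5.0, 5.1 or 5.2 followed by a week-6 value below 5.0. If the requirement in Treatment delivery covers week 1, this participant fails it, and the caption's bar at 5.3 is redundant. If it covers week 6 only, the two statements add together and the participant passes both. The text does not say which is meant.

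**Post-increase sample.** The caption places the increase at week 8, and 8 + 1 = week 9, which is the scheduled draw. With the ±7-day window that draw may fall in weeks 8 to 10. A week-8 draw followed by a week-9 start is therefore permitted. The next scheduled draw is week 12 ± 1, that is weeks 11 to 13, or 2 to 4 weeks after that start.

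**The case against.** The best defense is that the texts are complementary. The monitoring section would govern a single rise and its recheck, and rule 3 would add a limit on recurrence. The monitoring section never says that two consecutive draws are the *only* ground for discontinuation, and it returns participants to normal monitoring only while potassium stays below 5.3. Read this way, the recurrent case has one answer: removal. The reading is plausible, but no text states it. It also leaves the persistent case (5.4 then 5.5) open on removal, and it does not explain the risks section's wording. Figure 2 is not shown and is counted neither way.

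A reader might infer more than the article supports:

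- **That the dose-increase thresholds contradict each other.** The caption bars values of 5.3 or more at week 1. It does not say that 5.0 to 5.2 qualifies, and the two conditions can be cumulative. They also decide dose, not retention.
- **That the post-increase sample is planned too early.** Coordinators tell participants when to start the new capsules, and a week-8 increase fits the week-9 draw. The gap is a corner case that the mailing period and sampling window allow.
- **That sites will diverge, or that mainly one arm is affected.** Participants are recruited to one clinical center, and outside facilities only draw blood. Treatment is double-blinded. The 0.30 mmol/L median rise quoted in the risks section comes from left-heart-failure patients. No baseline potassium distribution is given, and this trial excludes potassium above 5 mEq/L at enrollment and several groups at higher risk of hyperkalemia. That rise cannot show how many participants would be affected in either arm.

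**Conclusion.** The point holds for potassium of 5.3 to 5.9 mEq/L that recurs or persists. The three texts do not yield one answer on whether drug continues after a non-consecutive recurrence, or on whether a participant with two consecutive high values is removed. The endpoint definition inherits both gaps, as well as the open question of temporary stops.

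The scope is limited. The rule at 6.0 or more and the handling of a single transient rise are consistent, the endpoint is a secondary safety endpoint, and the overall effect cannot be quantified from the article. The conclusion rests on reading each section literally, because no sentence links them. The dose-increase criterion and the timing of the post-increase sample need clarification but are not demonstrated contradictions. The stopping rule still merits correction because it bears on safety and on who counts as having discontinued.

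**What to change.** - Reconcile Spironolactone treatment, individual stopping rule 3 and the risks section into one rule. It should cover both persistent and non-consecutive recurrent values, define *episode*, and say whether the participant leaves the protocol or only stops drug.
- Define the hyperkalemia discontinuation endpoint in Study endpoints from that rule, and state whether temporary stops count.
- As secondary clarifications, reconcile the dose-increase criterion in Treatment delivery with the Figure 1 caption, naming the visits to which each applies. Also state how the week-9 draw relates to the actual start of the new capsules, so that it agrees with the article's own commitment to a sample one week after an increase.

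Which thresholds and which clinical rule to adopt is for the sponsor and clinicians. The cost is a protocol clarification, with matching edits to the figures or schedule where needed. No additional participants are required.

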**Figure 2 F2:**
[figure not shown]
**Monitoring plan for participants who develop hyperkalemia.** *Throughout the study, participants with a potassium level >5.0 mEq/L will undergo dietary counseling regarding a low potassium diet. **At the investigators’ discretion, any participant with a potassium level ≥5.3 mEq/L can be referred for medical evaluation at the nearest health care facility. Cr, creatinine; K, potassium; labs, laboratory tests.

#### Six-minute walk test

Throughout testing, all participants will be monitored by a respiratory therapist or a pulmonary function technician with pulse oximetry. The test will be terminated if the participant develops limiting clinical symptoms including but not limited to significant fatigue, shortness of breath, leg discomfort and dizziness.

#### Cardiopulmonary exercise testing

All participants will be accompanied by a pulmonary function technician and a licensed practitioner and will be monitored by continuous pulse oximetry and electrocardiography (ECG). Exercise testing will not be performed in participants with absolute contraindications to exercise testing according to American College of Cardiology/American Heart Association guidelines, which include the following: acute myocardial infraction (within 2 days), high-risk unstable angina, uncontrolled cardiac arrhythmias causing symptoms or hemodynamic compromise, symptomatic severe aortic stenosis, uncontrolled symptomatic heart failure, and acute aortic dissection. Determination of test termination will be based on published guidelines (Table 6) [64]. In addition, the test will be terminated regardless of symptoms if both of the following two conditions are met: pulse oximetry decreases by >5% from baseline and pulse oximetry value <90%.

**Table 6 T6:** American College of Cardiology/American Heart Association indications for terminating exercise testing

**Absolute indications**	**Relative indications**
1. Decrease in systolic blood pressure >10 mmHg from baseline, accompanied by evidence of ischemia	1. Decrease in systolic blood pressure >10 mmHg from baseline, in the absence of evidence of ischemia
2. Moderate to severe angina	2. ST or QRS changes such as excessive ST-depression (>2 mm of horizontal or down-sloping ST-segment depression) or marked axis shift
3. Increasing nervous system symptoms (ataxia, dizziness, or near-syncope)	
4. Signs of poor perfusion (cyanosis or pallor)	3. Arrhythmias other than sustained ventricular tachycardia, including multifocal PVCs, triplets of PVCs, supraventricular tachycardia, heart block, or bradyarrhythmias
5. Technical difficulties in monitoring ECG or systolic blood pressure	
6. Participant’s desire to stop	4. Fatigue, shortness of breath, wheezing, leg cramps or claudication
7. Sustained ventricular tachycardia	5. Development of bundle-branch block or IVCD that cannot be distinguished from ventricular tachycardia
8. ST elevation (≥ 1.0 mm) in leads without diagnostic Q-waves (other than V_1_or aVR)	6. Increasing chest pain
	7. Hypertensive response^a^

^a^In the absence of definitive evidence, the committee suggests systolic blood pressure of >250 mmHg and/or a diastolic blood pressure of >115 mmHg. ECG, electrocardiography; IVCD, intraventricular conduction delay; PVCs, premature ventricular contractions.

#### Magnetic resonance imaging

MRI scans are expected to last 30 to 60 minutes but may get prolonged to 90 minutes in some cases. Scans are monitored by a technologist supervised by a physician or by a physician with the support of a second health care professional. Monitoring typically includes continuous ECG, intermittent non-invasive blood pressure, and pulse oximetry as indicated. Participants may elect to terminate the imaging protocol at any time.

MRI studies will be monitored in the following ways: direct visual and auditory contact with the participant by a nurse, nurse practitioner or physician in the MRI suite; indirect visual contact via a video camera output displayed over the MRI scan control console; two-way microphone system between the participant and the operator of the MRI scan control console; continuous display of the ECG; and intermittent non-invasive measurement of blood pressure.

### Individual participant stopping rules

PAH is a progressive disease and therefore clinical worsening may occur in participants during the protocol, irrespective of their treatment group assignment. Individual stopping rules for participants enrolled in the protocol include:

1. If a participant develops clinical evidence of right heart failure (which may include but is not limited to elevated jugular venous pressure, ascites and lower extremity edema) as determined by the patient’s primary physician or the investigators, then the participant will be removed from the protocol and treated for decompensated right heart failure according to standard of care.

2. If a participant deteriorates clinically, even in the absence of overt right heart failure, and the primary treating physician or the investigators feel that the addition of a MR antagonist such as spironolactone or eplerenone is clinically indicated then the participant will be removed from the study.

3. If a participant has more than one episode of serious hyperkalemia (potassium ≥5.3 mEq/L) or one episode of severe hyperkalemia (potassium ≥6.0 mEq/L), the study drug will be discontinued and the participant will be removed from the protocol.

4. If a participant develops renal insufficiency (rise in serum creatinine >50% of baseline) while on protocol, then the study drug will be discontinued and the participant will be removed from the protocol.

5. In the event that testing for serum potassium, blood urea nitrogen and creatinine is delayed for >7 days, the participant will be instructed to stop the study drug and will be removed from the protocol.

6. In any participant with a serum potassium level ≥ 5.3 mEq/L, a delay in laboratory monitoring longer than 48 hours from the specified time frame will result in removal from the protocol.

7. If while on study drug a participant develops significant breast pain or gynecomastia then the study drug will be discontinued and the participant will be removed from the protocol.

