### Statistical considerations and analysis of the study

#### Sample size

Previous studies have examined the effects of PAH-specific therapy on time to clinical worsening, exercise capacity and endothelial inflammation in patients with PAH [59-63]. Moreover, the effects of spironolactone on endothelial dysfunction have been examined in diverse non-PAH patient populations [19-23]. However, no prior randomized controlled trials have been completed that report on the effects of spironolactone treatment in patients with PAH. Assuming that a subset of the participants with PAH may discontinue study drug or otherwise not be able to complete the study, we plan to enroll up to 70 participants with PAH to obtain at least 50 completed studies. The participants will be randomized in a 1:1 ratio to spironolactone therapy or placebo. At a two-sided α level of 0.05, we will have at least 84% power to detect an effect size (group mean difference divided by standard deviation) of 0.9 for the difference in the change of 6-minute walk distance from baseline between the two treatment groups [61].

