Gynecomastia in men and painful breast enlargement in women may occur in participants treated with spironolactone and appear to be related to dose and duration of therapy [67-69]. The Randomized Aldactone Evaluation Study reported incidences of gynecomastia and breast pain in 9% and 2% of spironolactone-treated patients, respectively. This was significantly different from placebo and led to discontinuation of the study drug in 2% of spironolactone-treated patients in this trial [15]. In the majority of cases, gynecomastia and breast pain subside with cessation of the drug [68,70]. Prior to initiation of the study drug and throughout the trial during follow-up visits, participants will be asked about the presence of breast pain and, in male patients, the development of gynecomastia. If while on the study drug a participant develops significant breast pain or gynecomastia then the study drug will be discontinued. Additional side effects reported with spironolactone therapy and related to its progesteronal and anti-androgenic activity include menstrual irregularities (amenorrhea, postmenopausal bleeding), decreased libido and erectile dysfunction [67-69]. These also appear to be dose related and typically resolve upon drug cessation [69,71].

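### Stopping study drug for side effects or a late safety test also ends participation, so week-24 walks are lost and clinical-worsening follow-up is cut short, possibly unequally between arms

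*Protocol article*

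**What the plan says.** **Removal rules.** Under Individual participant stopping rules, rules 3, 4, 5 and 7 each order two acts: study drug stops and the participant leaves the protocol. The triggers are repeated or severe hyperkalemia (rule 3), a creatinine rise above 50% (rule 4), a safety test more than 7 days late (rule 5) and breast effects (rule 7). For rule 5, "the participant will be instructed to stop the study drug and will be removed from the protocol". Rule 7 applies when a participant "develops significant breast pain or gynecomastia then the study drug will be discontinued and the participant will be removed from the protocol". Rule 6 orders removal, without mentioning study drug, when monitoring after a potassium of 5.3 mEq/L or more is over 48 hours late. The Spironolactone treatment subsection on monitoring and withdrawal repeats removal for late tests, potassium of 6.0 mEq/L or more, and creatinine.

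**Places that mention drug discontinuation only.** Risks associated with spironolactone therapy says of a participant who "develops significant breast pain or gynecomastia then the study drug will be discontinued" nothing about leaving the study. The Spironolactone treatment subsection likewise only discontinues drug when potassium stays at 5.3 mEq/L or more on two consecutive draws.

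**Sample size.** Non-completion is expected to include drug discontinuation: "Assuming that a subset of the participants with PAH may discontinue study drug or otherwise not be able to complete the study". The enrollment target allows for this loss: "we plan to enroll up to 70 participants with PAH to obtain at least 50 completed studies". Allocation between the arms is equal: "The participants will be randomized in a 1:1 ratio to spironolactone therapy or placebo".

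**Endpoints and analysis.** The primary endpoints are the 24-week change in 6-minute walk distance and the incidence of clinical worsening (Study endpoints). Study analysis uses a linear mixed model for the first and Kaplan-Meier curves with a log-rank test for the second. The only rule for informative missing data concerns VO2 maximum.

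**The concern.** Ending treatment and ending observation are different decisions, and these rules merge them. A raised potassium, a creatinine rise, breast symptoms or a late blood test does not in general stop someone walking for six minutes. Nor does it prevent recording death, transplantation, hospitalization or a new PAH drug. Yet as printed, such a participant contributes no week-24 walk and no clinical-worsening follow-up after removal.

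Risks associated with spironolactone therapy names hyperkalemia, renal insufficiency and gynecomastia with or without breast pain among the drug's main risks. Removal for these reasons may therefore be more frequent on spironolactone. If those removed also differ in outcome from those who stay, the walk comparison is no longer protected by randomization, and censoring in the log-rank comparison is informative. Outcomes not collected cannot be recovered by later analysis.

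**Working it through.** **1. The plan's own figure.** Sample size states: "At a two-sided α level of 0.05, we will have at least 84% power to detect an effect size" "of 0.9 for the difference in the change of 6-minute walk distance from baseline between the two treatment groups". Inputs: 25 completers per arm (50 at 1:1), effect 0.9 SD, two-sided alpha 0.05.
- Normal approximation: 0.9 × √(25/2) = 3.18; 3.18 − 1.96 = 1.22; power 88.9%.
- Noncentral t: 87.7%.

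The stated figure holds as a lower bound. The allowance for loss is 20/70 = 28.6%.

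**2. What follows from the text.** Removal before week 24, with no follow-up provided afterwards, means no week-24 walk. Serial testing is also planned at week 12, so a week-12 value may exist for the mixed model. Clinical worsening is observed until removal and then cut off.

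**3. How unequal loss becomes bias (illustration).** Let fA and fB be the fractions lost per arm, and let removed participants do k SD worse than completers. Each arm's completer mean is then too high by f × k, so bias = (fA − fB) × k. With nA and nB completers, SE = √(1/nA + 1/nB) in SD units. Take no true effect, 35 per arm and 20 lost in total; k and the splits are assumptions.

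| Split of losses | Bias, k = 0.5 to 1.0 | Type I error |
|---|---|---|
| 10/10 | 0 | 5.0% |
| 12/8 | 0.06 to 0.11 SD | 5.5% to 6.9% |
| 14/6 | 0.11 to 0.23 SD | 6.8% to 12.5% |
| 15/5 | 0.14 to 0.29 SD | 7.8% to 16.8% |

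For 14/6: fA − fB = 14/35 − 6/35 = 0.229. Multiplying by 0.5 and 1.0 gives 0.114 and 0.229 SD. SE = √(1/21 + 1/29) = 0.287. Across these splits, power at 0.9 SD stays at 86% to 88%, so the harm is bias rather than power. This compares completers only; a mixed model using week-12 values could recover part of it.

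**4. Late tests (lost numbers only).** Six safety tests precede week 24: day 7 and weeks 6, 9, 12, 16 and 20. If each has a 2% to 5% chance of being over 7 days late, independently (assumption; no rate is given), then 1 − 0.98⁶ = 11% and 1 − 0.95⁶ = 26% are removed. Week 12 is drawn at the NIH Clinical Center visit. Counting only the other five points gives 9.6% to 22.6%.

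**5. Power if everyone is followed.** With 35 per arm and no other loss:
- Effect stays at 0.9 SD: 96.5% (normal) or 96.0% (t).
- 5 of 35 on spironolactone stop and lose all benefit (assumption): 0.9 × 30/35 = 0.77 SD, power about 90% (normal).
- 10 of 35: 0.9 × 25/35 = 0.64 SD, power about 77% (normal).

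**The case against.** **The absence of follow-up is inferred.** No sentence forbids measuring outcomes after removal, no censoring rule is printed, and a fuller protocol or SAP may add both. This stands as a caution. But the printed rule is removal, not drug discontinuation alone, and Sample size counts drug discontinuation among the reasons for not completing.

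**A reader might infer that both primary outcomes go wholly unmeasured.** They do not: worsening is recorded up to removal, and a week-12 walk may exist.

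**A reader might infer a large one-sided loss from the gynecomastia incidence in the cited heart-failure trial.** The document does not support that. In that trial breast effects led to drug discontinuation in 2% of spironolactone patients, which is closer to what rule 7 describes and amounts to 0.7 of 35. PAH is also described as two to four times more common in women. Severe hyperkalemia there was 2% against 1%, or 0.7 against 0.35 of 35, and not significantly different. Exclusions for reduced eGFR, raised potassium and interacting drugs lower the risk further. No rates are given for potassium of 5.3 to 5.9 mEq/L or for creatinine removals. The possibility of imbalance stands; a large imbalance is not shown.

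**A reader might take the late-test range as a measure of bias.** It is not. The rule is the same in both blinded arms and nothing ties lateness under rule 5 to treatment. Rule 6 differs somewhat, because it applies only after a high potassium.

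**The Risks section is only a summary.** Leaving out removal there does not say that the participant stays. That is fair, but an investigator still meets two different instructions.

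**Conclusion.** The point holds as a design weakness that can be corrected cheaply. As printed, rules 3 to 7 forgo week-24 walks and later worsening events for reasons that include the drug's own named risks. Both primary comparisons can be biased if removals differ between arms and removed participants differ in outcome.

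Neither the size nor the direction of the bias can be determined from the document. The 0.11 to 0.23 SD and the 6.8% to 12.5% type I error rest on an assumed 14/6 split and an assumed outcome gap of 0.5 to 1.0 SD. An even split with the same gap gives no bias. Late tests under rule 5 mainly cost numbers, and the 11% to 26% is an assumption about those numbers alone. The stated power is not in error.

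**What to change.** 1. Leave every criterion for stopping study drug as it is.
2. In rules 3 to 7, and in the matching text of the Spironolactone treatment subsection, replace only the removal wording. State that the participant remains in follow-up for the scheduled week-12 and week-24 walk tests, and for clinical worsening to week 24, unless consent is withdrawn. Add no drug-stopping text to rule 6. Do not extend the change to the section on pregnant women.
3. Analyze participants as randomized, including data collected off drug, and say that this is the effect being estimated.
4. Reconcile the breast-effects text in the Risks section with rule 7. Reconcile the text on two consecutive potassium draws in the Spironolactone treatment subsection with rule 3. In each pair, the former mentions drug discontinuation only.

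**Cost.** A wording amendment and a consent sentence. The week-12 and week-24 visits are already in the schedule, and the trial is still recruiting. The statistical price is dilution of the on-treatment effect. It is not necessarily slight: in the 10-of-35 case above, power is below the stated 84%.
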